### Primary outcome measures

The primary outcome measure in this study will be the KOOS pain score (0–100 points). This measure will allow us to identify the overall treatment effect of the wedged insole intervention over the 3-month follow-up period.

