### Sample size calculation

Sample size calculations were performed based on our primary outcome variable, the KOOS pain score, with a desired power of 80% and a significance level of 0.05 using the statistical software Stata version 11.2. Given the early stage of research concerning the effects and interactions of load reduction, and different OA subtypes on treatment outcome, we chose to only conduct sample size calculations on a repeated measures basis for within group comparisons. Based on the results of this trial, sample sizes may be expanded to increase statistical power in order to make comparisons between the control and KAM-R group.

The minimum perceptible clinical improvement and minimum detectible change in KOOS score has been reported to be about 13.4 points [33, 41]. Using a baseline KOOS pain score of 57.3 points [42] and a standard deviation of 15 points [41], to detect a minimal clinically important improvement of 13.4 points within each group, 20 participants are required in each group, or 40 total participants. To account for a potential dropout rate of 15%, we will recruit a minimum of 46 participants.

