#### Within group analyses

All data will be analyzed on an intention to treat basis. Changes from baseline to 3 months will be assessed within groups for ordinal data (UCLA score) using Wilcoxon Signed Rank test (α = 0.05). KOOS subsection scores and PASE scores will be compared between baseline and at 3 months using paired-samples t-tests (α = 0.05). KAMs, KAM impulse, varus thrust, and footwear comfort will be compared between the neutral shoe and assigned wedged insole condition at baseline for the KAM-R group using paired-samples t-tests (α = 0.05). All tests will be two-tailed, except in the case of KAMs and KAM impulse, where one-tailed tests will be used. The reason for this is that KAM reduction is strictly controlled in this study and so KAM and KAM impulse reductions are the only possible outcome.

A multivariable linear regression (α = 0.05) will also be conducted on the KAM-R group to evaluate whether KAM reduction, KAM impulse, varus thrust and footwear comfort can predict change in pain over 3 months. Covariates tested in these four models will include adiposity and Kellgren-Lawrence grade.

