#### Between group analyses

Ordinal data from UCLA scores and Kellgren-Lawrence grades will be compared at baseline and at 3 months (UCLA score only) between the control and KAM-R group using Mann–Whitney U tests (α = 0.05). KOOS subsection scores, PASE scores, KAMs, KAM impulse, varus thrust, adiposity, footwear comfort, and adherence will be compared at baseline between the KAM-R and control group using a MANOVA test (α = 0.05) with independent-samples t-tests for post-hoc analysis. Changes over 3 months will also be assessed between groups using a MANOVA (α = 0.05) with independent-samples t-tests for post-hoc analysis. All tests will be two-tailed, except in the case of KAMs and KAM impulse, where one-tailed tests will be used. The reason for this is that KAM reduction is strictly controlled in this study and so a reduction in KAMs and KAM impulse is the only possible outcome. It should be noted that all between group comparisons are exploratory analyses, as we may not be powered to detect any significant differences between groups.

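### The between-arm comparison of KOOS change has no baseline covariate: valid over randomisations, but less precise than a baseline-adjusted model that needs no new data

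*Protocol article*

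**What the plan says.** Under the primary outcome heading: "The primary outcome measure in this study will be the KOOS pain score (0–100 points"). The Background section states the hypothesis as a between-group one: pain and function should improve more over 3 months in the KAM-R group than in the control group.

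The section on between group analyses uses the continuous scales in two ways:

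- At baseline, the KOOS subscales, PASE and several other variables "will be compared at baseline between the KAM-R and control group using a MANOVA test (α = 0.05) with independent-samples t-tests for post-hoc analysis". UCLA score and Kellgren-Lawrence grade are tested at baseline by Mann–Whitney.
- For the outcome, "Changes over 3 months will also be assessed between groups using a MANOVA" at the 0.05 level, followed by independent-samples t-tests.

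No covariate is attached to either. The only covariates named in the article belong to the regression within the KAM-R group: "Covariates tested in these four models will include adiposity and Kellgren-Lawrence grade". Randomisation is stratified by sex alone, so the design does not balance baseline pain.

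The same section adds a caveat on status: "It should be noted that all between group comparisons are exploratory analyses". The sample size section says its calculation was made for within-group comparisons.

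**The concern.** Analysing the change from baseline fixes the coefficient of the baseline score at 1. When the baseline and follow-up scores have equal spread, the regression coefficient of follow-up on baseline is r, which is below 1. The change score therefore subtracts too much of the baseline. This has two consequences:

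- The variance of the contrast is larger than it needs to be.
- An arm that starts higher by chance will tend to show a smaller gain, through regression to the mean.

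With about 20 participants per arm, chance differences of several KOOS points at baseline are ordinary.

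Meanwhile the baseline scores go into between-arm significance tests. In a randomised comparison such a test asks whether a difference arose by chance when allocation was by chance, and nothing in the plan depends on the answer.

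The randomised contrast is at stake. Change within an arm mixes any insole effect with regression to the mean and natural course. Only the comparison with the waitlist arm separates them, and the authors already doubt their power for it.

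**Working it through.** **Inputs from the sample size section.** A 13.4-point difference, "a standard deviation of 15 points", 20 per group, α = 0.05 and target power 80%. KOOS tests are two-tailed.

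**Inputs assumed.** The correlation r between baseline and 3-month KOOS pain is not given, so it is taken as 0.3 to 0.8. The SD is taken as 15 at both visits.

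**The plan's own figure.** The normal-approximation formula for two independent means with SD 15 and difference 13.4 gives 20 per group (power 80.6%; noncentral t gives 78.6%). The stated 20 reproduces this way. A one-sample or paired calculation with SD of change 15 would give 10 (normal) or 12 (t).

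**Formulas.**
- SD of change = 15√(2(1−r))
- Residual SD after baseline adjustment = 15√(1−r²)
- Variance ratio, adjusted to change = (1−r²)/(2(1−r)) = (1+r)/2
- SE of the contrast = SD × √(2/20)
- Shift of the change contrast for a baseline imbalance D = −(1−r)D

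**Chance imbalance.** The SE of the baseline difference is 15 × √(2/20) = 4.74 points, with a 95% range of about ±9.3.

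**Results, change score v baseline-adjusted (power by noncentral t):**

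| r | SE | Variance ratio | Power | Shift for a 1-SE imbalance |
|---|---|---|---|---|
| 0.3 | 5.61 v 4.52 | 0.65 | 64% v 82% | 3.3 points |
| 0.5 | 4.74 v 4.11 | 0.75 | 79% v 89% | 2.4 points |
| 0.7 | 3.67 v 3.39 | 0.85 | 94% v 97% | 1.4 points |
| 0.8 | 3.00 v 2.85 | 0.90 | 99.2% v 99.6% | 0.9 points |

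Allowing for estimation of the baseline slope lowers the adjusted power by about 1 point or less (81%, 88% and 97% in the first three rows).

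**Simulation (40,000 trials, true effect 13.4).** Over all randomisations both methods average 13.4. Among trials where the KAM-R arm starts about 4.74 points higher, the change contrast averages 10.1, 11.0 and 12.0 at r = 0.3, 0.5 and 0.7. The adjusted contrast averages 13.4 each time.

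**Sensitivity to the entry limit.** Eligibility requires KOOS pain of 75 or lower, which is (75 − 57.3)/15 = 1.18 SD above the assumed mean. If 57.3 and 15 describe an unselected normal population (an assumption), truncation at 75 cuts the baseline SD to about 12.4. Hold the slope at r and the residual SD at 15√(1−r²). The variance ratio at r = 0.3, 0.5 and 0.7 is then 0.73, 0.81 and 0.89. Change-score power is 69%, 82% and 95%, against an unchanged 82%, 89% and 97% after adjustment. The 1-SE shift is 2.7, 2.0 and 1.2 points.

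**The case against.** The strongest reply is that the planned analysis is valid. Three stronger readings are tempting, and the article does not support them:

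- **That the tests ignore baseline.** They do not. A change score subtracts baseline; what is missing is adjustment with an estimated coefficient.
- **That the contrast is biased.** It is biased only conditionally on the imbalance that happens to occur. Over randomisations it is unbiased, as the simulation shows.
- **That the baseline tests will raise a false alarm about half the time.** Counting 14 independent tests gives 1 − 0.95¹⁴ = 51%. But 12 of those sit behind one MANOVA, and five are subscales of one questionnaire, so independence is not credible. Treating the MANOVA and the two Mann–Whitney tests as three independent tests gives 1 − 0.95³ = 14%. The fault of these tests is that they serve no purpose, and no error rate needs to be claimed.

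Three further points carry weight. First, the t-tests follow a MANOVA on the changes and are not the whole comparison. That does not help, because the MANOVA analyses the same unadjusted changes. Second, the gain depends on inputs the documents do not give. It is negligible at r = 0.8. The article also does not say which quantity its SD of 15 describes: if it is the SD of change, the planned t-test has about 79% power. Third, the comparisons are declared exploratory, so no confirmatory claim rests on them.

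An unseen analysis plan might add covariates. That is only a partial defence, since the article itself names the tests and attaches none.

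**Conclusion.** The point stands as a free improvement in efficiency. It is not a finding of invalidity. As written, the between-arm comparison of KOOS and the other continuous scales gives up precision that the collected baseline scores would supply, and it leaves the estimate exposed to chance imbalance.

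Under equal SDs of 15 and 20 per arm, adjustment lowers the variance by 35% at r = 0.3, 25% at 0.5, 15% at 0.7 and 10% at 0.8. In power for 13.4 points, that is a gain of 18, 10, 3 and under 1 percentage points. If the entry limit narrows the baseline SD to about 12.4, the gain is about 13, 7 and 2 points at r = 0.3, 0.5 and 0.7. These sizes rest on the assumed r and SDs. The direction does not depend on which r in the range is right.

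The exploratory label lowers the formal weight but does not remove the point. This is the only randomised estimate, it carries the hypothesis in the Background section, and the sample size section says the trial may be expanded for this comparison on the strength of these results.

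**What to change.** In the section on between group analyses:

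1. For the continuous patient-reported scales, replace the MANOVA and t-tests on change by a linear model of the 3-month score on arm and the baseline score of the same scale. Put KOOS pain first. Report the adjusted difference with its 95% confidence interval.
2. Keep the statement that between-group comparisons are exploratory.
3. Replace the baseline MANOVA, its post-hoc t-tests and the baseline Mann–Whitney tests by a descriptive table by arm.

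The cost is one degree of freedom per model and a change of wording. No extra visits, measurements or participants are needed.

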Across 13 international clinical guidelines for management of knee OA, wedged insoles (i.e. insoles that elevate either the lateral or medial aspect of the foot) have been consistently recommended for disease management since they can influence KAMs [10]. On average across patients, laterally wedged insoles have been shown to reduce KAMs and reduce pain, while medially wedged insoles tend to increase KAMs; [4, 11] however, when considering subject specific reactions, 15-43% of patients, depending on the study, receiving either a medial or lateral wedge will experience KAM changes that are completely opposite to the group average result [12, 13]. This means that every year, thousands of North Americans with knee OA are being prescribed an incorrect wedge resulting in increased KAMs, and possibly accelerating and worsening their OA.

Interestingly, when reviewing past literature of major randomized trials for knee OA, no study has actually ensured that all patients experienced a reduction in KAMs in the experimental insole group, and this has likely had a large bias on study results [14, 15]. Thus, it is no surprise that a recent review has highlighted that large variability exists across studies in terms of the effectiveness of lateral wedge insoles [16]. Essentially, we still do not truly understand how or if wedged insoles and reduced KAMs can benefit patients with knee OA. Therefore a randomized trial is urgently needed that assigns wedged insoles on a personalized basis to ensure that KAMs are being reduced. Thus, the primary purpose of this study is to evaluate the effectiveness of a personalized wedged insole intervention on pain in patients with medial knee OA. Specifically, KAMs must be measured for each participant to ensure KAM reduction occurs with the intervention insole, rather than providing all patients with the exact same insole and assume a constant KAM effect as previous trials have done. This approach of ensuring KAM reduction has never been attempted before and so the results from this study will help evaluate the true clinical benefit of KAM reduction, and also the true effectiveness of wedged insoles. It is hypothesized that patients in the experimental group, where KAMs have been reduced using an individually prescribed wedged insole, will overall have greater improvements in pain and physical function over 3 months compared to the control group.

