### Eligibility, recruitment and evaluation for inclusion

The trial will have two parallel groups, where participants are randomly assigned to a waitlist control or experimental arm for a study duration of 3 months (Figure 1). Patients with painful radiographic medial knee osteoarthritis will be recruited from either the University of Calgary Sport Medicine Centre patient population (a Knee Osteoarthritis clinic is part of the services provided by this centre) or the Alberta Hip and Knee Arthroplasty clinics. Identified patients will be approached for inclusion into the study based on the inclusion/exclusion criteria described below. If recruitment is too slow to meet study timelines, advertisements of the project will be put into local newspapers and to other media. In these cases, a phone assessment of the volunteer will be undertaken for preliminary screening, and the individual will be invited for a detailed assessment by the study physician to determine their eligibility.

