**Flow of participants through the study.**

All patients considered eligible for the study must have physician-diagnosed knee OA primarily localized to the medial tibiofemoral compartment, based on the American College of Rheumatology clinical and radiographic diagnostic criteria [17]. Patients showing lateral compartment or patellofemoral OA in addition to medial knee OA will still be considered eligible as long as the medial compartment is the primary disease location and symptoms are attributed to the medial compartment. In addition, patients must be between the ages of 40–85 years of age, have no history of viscosupplement injections within the past 6 months, cortisone injection within the past 3 months, narcotic pain medication within the past 3 months, or use of other footwear insoles or unloader knee braces within the past 2 months, and must have a Kellgren-Lawrence grade (a measure of OA severity) of 1 to 3, as determined by a clinician, to avoid inclusion of end-stage OA patients that may be more appropriate for surgery [18]. Patients may continue to use anti-inflammatory medication or acetaminophen for mild pain management if needed. Those who meet the intrarticular injection criteria must also be willing to not undergo further treatment during the 3-month study. Patients must also present with a KOOS pain subscale score of 75 points or lower. This will help ensure that all participants have at least mildly painful knee OA. Any participant with recent (within 2 months) musculoskeletal or neuromuscular injury to the lower extremity that could bias pain assessments or gait analysis will not be considered eligible. For this reason, patients who typically use a cane will also be excluded.

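### The hypothesis compares KAM-R with control, but the plan has no confirmatory test of it: the trial is sized on within-group change and every between-group comparison is labelled exploratory

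*Protocol article*

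**What the plan says.** **Hypothesis and design.** The Background section predicts that the experimental group "will overall have greater improvements in pain and physical function over 3 months compared to the control group". Under Eligibility, recruitment and evaluation for inclusion: "The trial will have two parallel groups, where participants are randomly assigned to a waitlist control or experimental arm". Under Primary outcome measures: "The primary outcome measure in this study will be the KOOS pain score".

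**Sample size calculation.** The calculation was done "with a desired power of 80% and a significance level of 0.05", but "we chose to only conduct sample size calculations on a repeated measures basis for within group comparisons". The target is a 13.4-point improvement inside each group with an SD of 15. This gives 20 per group, and 46 are to be recruited to allow for 15% dropout. Comparing the arms is left to a possible later enlargement of the sample.

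**Within group analyses.** "KOOS subsection scores and PASE scores will be compared between baseline and at 3 months using paired-samples t-tests".

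**Between group analyses.** Changes over 3 months are compared by MANOVA with post-hoc independent t-tests. The section then adds that "all between group comparisons are exploratory analyses, as we may not be powered to detect any significant differences between groups".

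**Entry criterion on the primary outcome.** "Patients must also present with a KOOS pain subscale score of 75 points or lower".

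**The concern.** The comparison that the hypothesis names is the one the plan downgrades. The comparison it sizes for, change within an arm, is not what the hypothesis is about. It also sets the control arm a 13.4-point target that nobody predicts. If both arms improved by 13.4 points, both within-group tests would be expected to succeed although the treatment effect was zero.

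Change in KAM-R alone mixes any insole effect with natural fluctuation, use of the permitted analgesics and regression to the mean, since patients enter on a ceiling for the primary outcome itself. The contrast between randomised arms removes whatever of this is common to both. At stake is an efficacy claim resting on an uncontrolled pre-post test, or on significance in one arm and not the other. The Conclusions section already says that the study isolates the effect of reduced KAMs.

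**Working it through.** **Inputs from the protocol:** difference 13.4, SD 15, two-sided alpha 0.05, power 80%, 20 per group. The Sample size calculation does not say whether 15 is the SD at one time point or of the change, and gives no pre-post correlation r. **Assumed here:** r from 0 to 0.8, equal SDs at both time points, and non-specific change of 5, 7 or 10 points.

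**1. The plan's own figure.**
- Two-sample formula: n = 2 × (1.960 + 0.842)² × 15² / 13.4² = 19.67, so 20 per group.
- Paired formula with 15 as the SD of change: (1.960 + 0.842)² × 15² / 13.4² = 9.84, so 10.
- Paired formula with 15 per time point: the SD of change is 15 × √(2(1 − r)). Only r = 0 (SD 21.2) returns 20.

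So 20 per group reproduces either as a two-sample calculation or as a paired one at zero correlation.

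**2. How often the KAM-R paired test is significant with no insole effect.** Noncentral t, 19 degrees of freedom, noncentrality δ × √20 / SD of change, where δ is the non-specific change:

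| SD of change | δ = 5 | δ = 7 | δ = 10 |
|---|---|---|---|
| 15 (15 is the SD of change, or per time point with r = 0.5) | 29% | 51% | 81% |
| 21.2 (15 per time point, r = 0) | 17% | 29% | 52% |
| 9.5 (15 per time point, r = 0.8) | 61% | 88% | 99% |

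**3. Significance in exactly one arm,** when both arms change by the same 5 points: 2p(1 − p).
- SD of change 15: 2 × 0.293 × 0.707 = 41%.
- SD of change 21.2: 2 × 0.17 × 0.83 = 28%.

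**4. Power of the randomised comparison.** 20 completers per arm, 13.4 points, 15 as the SD per time point. Noncentrality is 13.4 / (s × √(2/20)).
- Change-score t-test: s = 15 × √(2(1 − r)), 38 degrees of freedom.
- ANCOVA: s = 15 × √(1 − r²), 36 degrees of freedom (40 less intercept, arm, baseline and sex).

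| r | Change-score t-test | ANCOVA |
|---|---|---|
| 0 | 49% | 78% |
| 0.3 | 64% | 82% |
| 0.5 | 79% | 89% |

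**5. A smaller net difference.** If KAM-R gains 13.4 points and controls gain 5, the difference is 8.4. ANCOVA power is then about 41% at r = 0 and 51% at r = 0.5.

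**The case against.** The authors declare the choice. They call the research early-stage, foresee a larger sample and warn of low power. That is fair, but disclosure does not reconcile the choice with a comparative hypothesis, or with a primary outcome that is said to show the overall treatment effect.

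A reader might infer more than the document supports:

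- **That the trial cannot answer its question.** A between-group test of 3-month changes is planned, and 20 per arm is also the two-sample number for 13.4 points at SD 15. The fault is mainly in the status given to the comparison, not necessarily in the number of patients.
- **That paired t-tests are the only analyses not called exploratory.** The within-group section also has a Wilcoxon test and a regression of pain change on KAM reduction in KAM-R. The Discussion offers that regression as some insight into placebo effects. It uses one arm and is not a randomised comparison, so it does not test the hypothesis.
- **That the randomised contrast would remove every bias.** Controls know that they have no insole, and the protocol says that placebo is not controlled for. Open-label placebo response stays in both analyses.
- **That large non-specific change is established.** The 5, 7 and 10 points are assumptions. The one part that can be approximated is regression to the mean from the entry ceiling. With z = (75 − 57.3)/15 = 1.18, it is 15 × φ(1.18)/Φ(1.18) × (1 − r) = 3.39 × (1 − r), or 0.7 to 1.7 points for r of 0.8 to 0.5. That alone raises the rejection rate to only about 5.5% to 7.7% at an SD of change of 15. It also treats 57.3 as a mean before selection, while the protocol calls it a baseline score. The point does not depend on this figure.

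**Conclusion.** The point holds in this form: the plan contains no confirmatory test of its stated hypothesis, and the analyses it was sized for could support an efficacy claim that the design does not protect. It should be corrected before analysis, because it concerns the primary inference.

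That conclusion follows from the text and needs no assumed figure. Its size does. Across the three readings of the SD, a non-specific change of 5 points makes the KAM-R test significant 17% to 61% of the time, and one of 10 points 52% to 99%. The stated reason for the demotion, possible lack of power, is weaker than it looks. Baseline adjustment gives about 78% to 89% for 13.4 points with 20 completers per arm, if 15 is the SD per time point and r is 0 to 0.5. Power for smaller differences is lower.

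**What to change.** 1. Name one primary analysis: the between-arm difference in KOOS pain at 3 months, by ANCOVA adjusted for baseline KOOS pain and sex (the randomisation stratum), two-sided alpha 0.05, with a 95% CI.
2. Define its population as the intention-to-treat main-study population: randomised patients who meet the KAM-reduction requirement, which is assessed in both arms from baseline data. Asking for every randomised patient would conflict with the Blinding section, which excludes those without a KAM reduction after randomisation. It would also need follow-up that the article does not plan.
3. Let this analysis replace the MANOVA step for KOOS pain only. Keep the exploratory label for the other between-group comparisons; deleting the sentence outright would lift it from all of them.
4. Call the within-group tests descriptive.
5. In the Sample size calculation, state whether 15 is the SD per time point or of change, and give the assumed correlation and between-arm difference.

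The cost is protocol wording, with no new patients or data. The downside is lower power if controls also improve (about 41% to 51% for a net 8.4 points). The confidence interval would show that uncertainty, whereas a pre-post p-value would hide it.
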